### Timeline

2.14

Our estimated timeline is presented in Fig. 1.

**Fig. 1 fig1:**
[figure not shown]
STIM hips timeline.

### Data management

2.15

Data will be managed in accordance with existing National Health and Medical Research Council of Australia (NHMRC)/Edith Cowan University policies.

### Risk management

2.16

Risk management for this RCT will be executed using the comprehensive Edith Cowan University risk management framework and reporting system (RiskWare). This system must be completed for ethical approval and involves logging details of actions such as completion of TMS or tDCS training for the clinical trial coordinator or engineering maintenance of TMS equipment. RiskWare is managed by the university risk management team who will support this research project.

## Analysis

3

### Statistical analysis

3.1

All data will be described at baseline and across each time point. Data distributions will be examined for each outcome using Shapiro Wilk test and guide preliminary statistical between group test selections. Repeated mixed effects models will determine between-group differences for the primary outcome (iHOT-33), accounting for relevant confounders (i.e., age; sex; BMI; radiographic severity) with relevant model assumptions examined. Secondary analysis will determine between-group differences for the other outcomes of interest (cortex excitability and CPM). Results will be reported according to EQUATOR Network reporting guidelines which include SAMPL and CONSORT. Statistical analysis will be performed by a blinded biostatistician from a separate institute.

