**Analysis:**

Data distributions will be examined for each outcome and guide preliminary statistical between group test selections. Repeated mixed effects models will determine between-group differences for the primary outcome (iHOT-33), accounting for relevant confounders (i.e., age; sex; body mass index; radiographic severity) with relevant model assumptions examined. Secondary analysis will determine between-group differences for the other outcomes of interest (cortex excitability and conditioned pain modulation).

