### Outcome measures

2.10

All baseline assessments will be completed within 7-days prior to commencing the intervention and follow-up will occur as per our assessment schedule (Table 3). Self-reported outcome measures will be recorded *via* RedCap® and will take 20–30 ​min for each participant. Physical assessment measures will be recorded by the principal investigator and research assistant directly into RedCap®. Physical assessments will occur at the Edith Cowan University neurophysiology laboratory, in accordance with existing standard operating procedures, and are expected to take ∼120 ​min.

**Table 3 tbl3:** STIM-Hips study assessment schedule.

	Variable	Weeks			
		0	4	8 (post-intervention)	16
Primary outcome variable	The International Hip Outcome Tool–33	x	x	x	x
Secondary outcome variables	Motor cortex excitability	x		x	
	Voluntary activation	x		x	
	Conditioned pain modulation	x		x	
	EuroQol 5 dimensions	x	x	x	x
Other variables	Demographics	x		x	
	Kellgren Lawrence (KL) Score	x			
	Scoring hip osteoarthritis with MRI (SHOMRI)	x			
	Flare-Osteoarthritis questionnaire	X	X	X	X
	Sit to stand pain	x		x	
	Muscle strength	x		x	
	Medication	x	x	x	x
	Physical activity	x	x	x	x
	Work status	x	x	x	x
	Dietary intake	x			
	Lifestyle Measures	x			
	Psychological Measures	x			
	Adherence	Continual			
	Adverse events	Continual			

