##### Pain, Disability and QoL

2.10.1.1

The International Hip Outcome Tool–33 (iHOT-33) is a valid and reliable tool to assess pain, disability and quality of life in people with hip OA, and recommended by the 2018 Zurich consensus [17]. The iHOT-33 has a range of scores from 0 to 100 and a minimal important change (MIC) of 12.5 points [18].

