### Power calculation

2.13

Using G∗Power v3: *n* ​= ​64 is sufficient to detect between-group differences if greater than the iHOT-33 MIC ​= ​12.5 points (*d* ​= ​0.71) [19], *α* ​= ​0.05, 1-*β* ​= ​0.80. Thus, we will recruit *n* ​= ​78 hip OA participants (*n* ​= ​39 per arm) accounting for an expected portion being lost to follow-up (drop-out ∼20% expected from pilot studies in knee OA [6]).

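### The primary model's closed covariate list leaves out baseline iHOT-33 and the text does not say how week 0 enters the model; unless a common baseline mean is used, precision is forgone

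*Protocol article*

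**What the plan says.** Section 3.1 (Statistical analysis) sets the primary analysis: "Repeated mixed effects models will determine between-group differences for the primary outcome (iHOT-33"). It then names what the model adjusts for: "accounting for relevant confounders (i.e., age; sex; BMI; radiographic severity) with relevant model assumptions examined". The Analysis paragraph of the abstract repeats the same four items: "accounting for relevant confounders (i.e., age; sex; body mass index; radiographic severity) with relevant model assumptions examined". In both places i.e. introduces the list, so it reads as complete, not as a set of examples.

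Table 3 in section 2.10 (Outcome measures) marks iHOT-33 at weeks 0, 4, 8 and 16, and the text above it says "All baseline assessments will be completed within 7-days prior to commencing the intervention". The baseline score is therefore planned for every participant.

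Section 2.13 (Power calculation) treats the trial as a simple two-group comparison: "64 is sufficient to detect between-group differences if greater than the iHOT-33 MIC" of 12.5 points, with d = 0.71, alpha 0.05 and power 0.80. It recruits "78 hip OA participants" to allow for about 20% loss. No credit is taken for baseline.

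The article does not say what part week 0 plays in the model, or whether the treatment effect is a main effect, a group-by-time interaction or a contrast at one visit.

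**The concern.** The baseline value of an outcome is usually the strongest single predictor of its later values. Here it is collected and then not named in the one place where the article lists what the primary model adjusts for.

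The consequence depends on how week 0 is used:

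- **Week 0 left out, or arms compared directly at follow-up.** The estimate gains nothing from baseline, and any chance difference between the arms at week 0 passes partly into the result.
- **Week 0 as an outcome with free arm means, and a change-from-baseline contrast.** Imbalance is subtracted in full, which over-corrects when r is below 1, and the standard error is larger than with baseline adjustment.
- **Week 0 as an outcome with a common baseline mean.** Precision equals that of baseline adjustment and nothing is lost.

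Only the third route is fully efficient without baseline as a covariate, and section 3.1 does not mention it. The trial is sized close to its 80% target, so forgone precision matters.

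**Working it through.** **Inputs.** From section 2.13: a target of 12.5 points, d = 0.71, alpha 0.05 (taken as two-sided, which reproduces the stated size; one-sided gives 25 per arm), power 0.80, 64 evaluable, 78 recruited, loss about 20%. From section 2.8: 1:1 allocation. The implied SD is 12.5 / 0.71 = 17.6 points. The correlation r between baseline and follow-up iHOT-33 is not in the document; I assume 0.3 to 0.7. I also read d = 0.71 as based on the SD of raw scores, which section 2.13 does not state.

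**Reproducing the plan's figure.** Normal approximation: 2 × (1.96 + 0.842)² / 0.71² = 31.1, so 32 per arm, 64 in total, as stated. With the noncentral t, 32 per arm gives 79.8% power and 33 per arm (66) is needed for 80%. Completers after 20% loss: 78 × 0.80 = 62.4, about 31 per arm.

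**Variance of the arm difference, relative to using follow-up scores alone.**

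- No baseline: 1
- Change score: 2(1 − r)
- Baseline-adjusted: 1 − r²

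Adjusted over change score is (1 − r²) / [2(1 − r)] = (1 + r) / 2, which is below 1 for every r below 1.

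**Power at 31 per arm.** Noncentral t with noncentrality δ × √(31/2), where δ is 0.71, 0.71/√[2(1 − r)] or 0.71/√(1 − r²), and 60, 60 or 59 degrees of freedom.

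| r (assumed) | No baseline | Change score | Baseline-adjusted |
|---|---|---|---|
| 0.3 | 78.5% | 64.2% | 82.2% |
| 0.5 | 78.5% | 78.5% | 88.8% |
| 0.6 | 78.5% | 86.8% | 93.0% |
| 0.7 | 78.5% | 94.4% | 97.1% |

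The change score matches the no-baseline analysis only at r = 0.5; below that it is worse.

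**Check within a repeated-measures model.** Standard error of the week 8 arm difference in points, by generalised least squares, with 32 per arm, SD 17.6, compound symmetry and weeks 0, 4, 8 and 16:

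| Specification | r = 0.3 | r = 0.5 | r = 0.7 |
|---|---|---|---|
| Follow-up visits only | 4.40 | 4.40 | 4.40 |
| Week 0 as outcome, free means, arms compared at week 8 | 4.40 | 4.40 | 4.40 |
| Week 0 as outcome, free means, change contrast | 5.21 | 4.40 | 3.41 |
| Week 0 as outcome, common baseline mean | 4.20 | 3.81 | 3.14 |

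The last row equals 4.40 × √(1 − r²), the result of baseline adjustment. Including week 0 as an outcome is therefore not enough; the common mean produces the gain.

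**Chance imbalance.** One standard error of the baseline difference at 32 per arm is 17.6 × √(2/32) = 4.4 points. In the first two rows such an imbalance shifts the estimate by r × 4.4, that is 1.3, 2.2 or 3.1 points at r = 0.3, 0.5 or 0.7. In the change contrast it shifts the estimate the other way by (1 − r) × 4.4, that is 3.1, 2.2 or 1.3 points.

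**The case against.** The strongest reply is that the list covers confounders, not the whole model. In a repeated mixed model week 0 can be a response row and would then not appear among covariates. A constrained-baseline model fits the published wording and loses nothing. A condensed article may leave the role of week 0 to an analysis plan, and section 2.2 says that statistical plans are registered. This stands in part: a reader might infer that the trial is committed to losing precision and leaving imbalance uncorrected, and the text does not support that. It does not state that week 0 is excluded. What remains is that the article did not defer its covariates: it enumerated them twice, in closed form and without baseline, and adding baseline later would depart from that list.

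The size is also open to challenge. Every r is assumed. The four listed covariates may already explain some of the same variance, and the calculation credits them with nothing. It takes one visit and completers only, whereas a mixed model also uses participants with partial follow-up. These limits stand, so the power figures illustrate the possible gain and do not forecast it.

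Finally, a reader might infer bias or a wrong sample size. Neither follows. Randomisation keeps the comparison unbiased on average without baseline, and the 64 was derived for an unadjusted comparison and reproduces.

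**Conclusion.** The point holds as a matter of efficiency and of an unstated model choice. The primary covariate list is closed and omits a baseline score that the trial schedules for every participant, and nothing in the article secures the one longitudinal specification that would make the omission harmless.

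If week 0 is ignored or the arms are compared directly at follow-up, power at 31 per arm is 3.7 to 18.6 percentage points below the baseline-adjusted figure for r from 0.3 to 0.7 (82.2 − 78.5 and 97.1 − 78.5). If change scores are used, the shortfall is 18.0 points at r = 0.3 and narrows to 2.7 at r = 0.7 (82.2 − 64.2 and 97.1 − 94.4). If a common baseline mean is used, there is no shortfall. These sizes rest on the assumed r, on d = 0.71 as a raw-score effect and on no contribution from the listed covariates; the last makes them likely upper figures. This is a worthwhile improvement at almost no cost, not a threat to validity.

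**What to change.** Before unblinding, state in section 3.1, and match in the abstract and the registered statistical plan, one of the following:

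- iHOT-33 at weeks 4, 8 and 16 is analysed in a mixed model for repeated measures with arm, visit, arm by visit, baseline iHOT-33 and baseline by visit, plus age, sex, BMI and radiographic severity; or
- iHOT-33 at weeks 0, 4, 8 and 16 is analysed in a constrained-baseline longitudinal model, with week 0 as an outcome and one baseline mean common to both arms, plus the same four covariates.

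Either wording also settles how week 0 enters the model. The cost is one sentence. The first option uses three degrees of freedom over three visits (one for baseline, two for its interaction with visit). No further data or participants are needed, and the sample size need not change.

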### Economic analysis

3.2

Participants will have no out-of-pocket costs. However, usual financial costs ($AUD) associated with tDCS usage and supervised physiotherapy (if participants had not been included in the trial and had to pay market rates) will be recorded using market average. Furthermore, market average costs from reported medications will be included. A subsequent economic evaluation with the healthcare system as the agent subject to costs, will estimate the incremental cost associated with the intervention per quality-adjusted life year using the EQ-5D-5L.

### Process evaluation

3.3

Implementation appraisal will occur following data collection (e.g., after the 16-week follow-up). STIM HIPS participants will be invited to small focus group interviews until saturation is reached. By exploring participant tDCS experiences, perceived barriers/facilitators to implementation will be identified. A qualitative descriptive study approach will be used to focus research questions directly on participant experience, as in our previous research [33,34]. QSR NVIVO will be used for coding and analysing the qualitative data using a deductive thematic approach. Results will be reported according to the consolidated criteria for reporting qualitative research (COREQ) [35].

## Implications

4

Given the massive worldwide prevalence, and that one-in-eleven Australians suffer from OA [36], it has been recognised within the Australian national OA strategy that immediate action is needed to reduce the personal, workforce and healthcare burden of this disease [37]. However, this is not a simple task, and OA is just one part of the picture. Australians with OA are twice as likely to report having ‘poor health’ versus those without [36]. Furthermore, these Australians typically present with several chronic health conditions (e.g., lower back pain, mental health complaints, cardiac disease or diabetes) [36] associated with decreased function and poor QoL. Therefore, even with the invention of a magic bullet to resolve OA pain, the impaired function and poor QoL would be unlikely to meaningfully change. Thus, interventions must be prioritised that can address pain, but also function and quality of life. An abundance of research details the benefits to pain, function and QoL from regular physical activity and good nutrition in conditions such as OA, cardiac disease and diabetes [38]. However, people with hip/knee OA have a significantly reduced level of physical activity compared to the general population [39]. These reduced levels of physical activity are, in part, due to fear that increased physical activity will make OA pain worse [40]. Unfortunately, this is a maladaptive response and further reductions in physical activity only serve to increase symptoms and reduce QoL.

The tDCS intervention described in this study protocol aims to address pain, function, and QoL in people with hip OA. tDCS has been demonstrated to reduce pain in people with OA [6,7]. Capitalising on the potential reduction of pain will also enable people with OA to increase their physical activity levels, providing the benefits of tDCS by relieving pain, and the associated benefits of increased physical activity. Furthermore, muscle strength can be increased during tDCS through altered cortical activity. As this should allow exercise with higher loads, enhanced muscular adaptation secondary to tDCS application should translate to greater strength improvement with training in people with hip OA. For example, if a leg press weight of 30 ​kg was required to improve muscle mass (hypertrophy) in an individual but voluntary activation deficits and cortical inhibition meant they were only able to provide 25 ​kg of force, they would be highly unlikely to increase muscle mass, which is a primary aim of rehabilitation. The adjunct use of tDCS is hypothesised to be able to overcome this barrier, and when applied, allow the person to produce 30 ​kg of force their muscle is more than capable of generating, but their brain was stopping them from accessing. Thus, tDCS will improve hip-related pain, disability and QoL *via* three mechanisms (Fig. 2): 1) directly reducing pain through tDCS application, 2) increased physical activity levels due to reduced pain from tDCS application, and 3) enhanced outcomes from rehabilitation due to additional muscular adaptation by using tDCS to reduce cortical inhibition.

**Fig. 2 fig2:**
[figure not shown]
Visualisation of the effect of tDCS.

Finally, the prevalence of hip OA is increasing at a significantly faster rate than knee OA [2] but the majority of the research is focussed on interventions for knee OA. Whilst that may not seem important, equity concerns exist as women have a far higher burden of hip OA than men [41]. However, this is unsurprising as women, including research into musculoskeletal conditions and treatment affecting women, have traditionally been substantially under-represented in sport science, physiotherapy and medical research [42]. The STIM Hips trial will address these research gaps by investigating a novel intervention to address pain, function and QoL in people with hip OA.

